## Abstract

**Background:**

Young people in low- and middle-income countries encounter significant barriers to accessing mental health support due to various factors, including a substantial treatment gap and limited health care budgets allocated to mental health. Using innovative strategies, such as scalable digital self-help psychological interventions, offers a potential solution for improving access to mental health support. However, digital mental health interventions come with their own set of challenges, including issues related to low user engagement. Chatbots, with their interactive and engaging nature, may present a promising avenue for the delivery of these interventions.

**Objective:**

This study aims to explore the effectiveness of a newly developed World Health Organization (WHO) digital mental health intervention, titled Scalable Technology for Adolescents and Youth to Reduce Stress (STARS).

**Methods:**

A single-blind, 2-arm randomized controlled trial will be conducted nationally across Jordan. Participants will include 344 young adults, aged 18-21 years, currently residing in Jordan. Inclusion criteria are heightened levels of psychological distress as determined through the 10-item Kessler Psychological Distress Scale (≥20). Assessment measures will be conducted at baseline, 1-week post intervention, and 3-month follow-up. Following baseline assessments, eligible participants will be randomized to receive STARS or enhanced usual care. The primary outcomes are the reduction of symptoms of depression and anxiety (Hopkins Symptom Checklist, 25 subscales) at 3-month follow-up. Secondary outcomes include general functioning (WHO Disability Assessment Schedule 2.0), well-being (WHO-5 Well-Being Index), personal problems (Psychological Outcomes Profile), and agency (State Hope Scale subscale).

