#### Primary Outcome

The primary outcome will be levels of depression and anxiety as determined through the HSCL-25 [39]. The HSCL-25 is a 25-item questionnaire consisting of 2 subscales assessing symptoms of depression and anxiety; 15 items correspond to symptoms of depression and 10 correspond to symptoms of anxiety. The validity and psychometric properties of the questionnaire have been well established in both adults and youths or adolescents [49,50]. Additionally, an Arabic version of the HSCL-25 has been previously validated [51] and has been used successfully among adults in Jordan during a previous study determining the effectiveness of a scalable psychological intervention [52].

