### Sample Size

A total of 344 participants will be included in the RCT. This sample size calculation was based on the results of prior trials exploring the effectiveness of comparable digital interventions which report effect sizes (Cohen *d*) ranging from 0.48 to 0.56 [17,18,59]. In addition, a similar effect size was used to determine the sample size for a similar RCT observing the effectiveness of a WHO-developed digital health intervention, based on a conservative, yet clinically significant effect size of 0.5 [60]. Assuming an effect size of 0.5 at a 3-month follow-up (power=90%; α=0.05, 2-sided), the trial would require 172 participants (STARS=86 and EUC=86). Given the high attrition rates reported in digital intervention studies, a conservative attrition rate of 50% was assumed. This attrition rate was informed by the results of the feasibility RCT and comparisons with protocols for similarly designed studies.

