### Statistical Analysis

To measure baseline differences between the 2 treatment arms, 2-tailed *t* tests will be conducted for continuous variables and chi-square tests for categorical data. To determine the effectiveness of the STARS intervention, intention-to-treat analysis will be conducted to compare the mean difference between STARS and EUC at baseline, post intervention, and 3-month follow-up. Differential change over time between treatment arms will be assessed using linear mixed models that accommodate missing data at subsequent assessments and provide differential slopes of trajectories between conditions. Hierarchical linear models study treatment effects because this allows the number of observations to vary between participants and handles missing data by using maximum likelihood estimation methods. Missing data will be assumed to be random if participants retained and not retained at 3 months do not differ on baseline characteristics. Fixed (intervention and time of assessment) effects and their interactions will be entered in unstructured models to yield indices of the relative effects of the treatments; time of assessment included baseline, post treatment, and 3-month follow-up. Analyses will focus on the primary outcome and secondary measures, with the main outcome time point being the 3-month follow-up relative to baseline. A subsequent per protocol completers analysis will be conducted, only including those who completed the 3-month follow-up, in order to assess the robustness of the primary analysis.

In addition to these analyses, the role of potential moderators and mediators, such as agency, on outcomes will be explored independently using the PROCESS macro. Two-tailed tests with a significance level of *P*<.05 will be reported for all analyses.

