## Discussion

### Brief Summary

Given the immense mental health treatment gap that exists globally, which is more pronounced in LMICs, scalable psychological interventions that can alleviate psychological distress and symptoms of mental health conditions are needed. This is particularly critical for youths, as they often face reduced access to mental health services due to the stigma associated with seeking help and the fact that many existing services are primarily designed for adults.

Digital health solutions can be particularly useful in bridging this gap. This study intends to contribute to the ongoing efforts of developing and evaluating potentially effective digital mental health solutions to minimize the mental health treatment gap by exploring the effectiveness of a novel digital mental health intervention in the form of a chatbot. The goal of this trial is to conduct a single-blind, 2-armed RCT among 344 young adults aged 18-21 years with heightened psychological distress in Jordan to evaluate the effectiveness of a newly developed WHO digital mental health intervention (STARS) in reducing symptoms of depression and anxiety versus EUC. STARS uses an engaging format to provide education and techniques to help reduce psychological distress, such as symptoms of depression and anxiety experienced by youths and adolescents. Recruitment for the trial began on July 16, 2023. Should the intervention demonstrate a decrease in symptoms of depression and anxiety at 3-month follow-up, it would support the potential for implementation of this new scalable psychological intervention for young people. Results from this trial are expected to expand the current range of available scalable psychological interventions.

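### The article does not settle whether there is one primary outcome or two, yet fixes P<.05 throughout and powers a single unnamed comparison; a success rule is needed to match error and power to the claim

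*Protocol article*

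**What the plan says.** The protocol article describes the primary outcome in several places, and they do not agree.

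- Abstract, Methods (plural): "The primary outcomes are the reduction of symptoms of depression and anxiety (Hopkins Symptom Checklist, 25 subscales) at 3-month follow-up".
- Methods, Primary Outcome (singular): "The primary outcome will be levels of depression and anxiety as determined through the HSCL-25". The same section describes the instrument as "consisting of 2 subscales assessing symptoms of depression and anxiety; 15 items correspond to symptoms of depression and 10 correspond to symptoms of anxiety". No total score is named there or elsewhere.
- Methods, Statistical Analysis (singular again): "Analyses will focus on the primary outcome and secondary measures, with the main outcome time point being the 3-month follow-up relative to baseline". It then sets one level for everything: "Two-tailed tests with a significance level of *P*<.05 will be reported for all analyses".
- Methods, Sample Size: "Assuming an effect size of 0.5 at a 3-month follow-up (power=90%; α=0.05, 2-sided), the trial would require 172 participants", that is, 86 per arm, doubled to 344 for 50% attrition. The section does not say which HSCL-25 score the effect size refers to.
- Discussion, Brief Summary, on what would support implementation: "Should the intervention demonstrate a decrease in symptoms of depression and anxiety at 3-month follow-up".

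No section says whether a significant result on one subscale is enough or whether both are needed.

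**The concern.** The number of primary outcomes and the rule for success determine what the 5% error rate and the 90% power refer to. As the text stands, an analyst could compare the arms on depression, on anxiety or on a combined score, each at .05, and decide afterwards which result makes the trial positive.

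If two subscales are tested and either may carry the claim, the chance of a false-positive primary result exceeds 5%. If both must succeed, the chance of success is below the stated 90%. These consequences belong to different rules and cannot both apply to one rule.

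The definition of success has practical weight. The Scalability of STARS and Conclusions sections tie open release of the intervention to positive findings from this trial and a second one.

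**Working it through.** **Inputs from the article.** d = 0.5, two-sided alpha 0.05, power 90%, 86 per arm, 1:1 allocation, 50% attrition, 344 randomized.

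**Assumptions.** The correlation rho between the two subscale test statistics is not given, so a range of 0 to 0.9 is shown. Where both subscales are considered, d = 0.5 is assumed on each.

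**Step 1. The plan's own figure.** A two-sample t-test with d = 0.5, alpha 0.05 and 90% power needs 85.03 per arm, rounded up to 86. Power at 86 per arm is 90.3% (normal approximation 90.6%). Then 172 / (1 − 0.5) = 344. The stated sample size is reproduced, as that of one test at .05.

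**Step 2. Either subscale suffices, each at .05.** The familywise error is 1 − P(|Z1| ≤ 1.96 and |Z2| ≤ 1.96) under the null, with (Z1, Z2) bivariate normal. At rho = 0 this is 1 − 0.95² = 9.75%.

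**Step 3. Both subscales required, each at .05.** Each Z has mean 0.5 × √(86/2) = 3.279. Joint power is P(Z1 > 1.96 and Z2 > 1.96). At rho = 0 this is 0.9064² = 82.2%.

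**Step 4. Holm at familywise .05.** The smaller p-value is tested at .025 (critical value 2.241). If it is significant, the other is tested at .05.

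- At least one significant: P(max(Z1, Z2) > 2.241).
- A given subscale significant: P(Z1 > 2.241) + P(1.96 < Z1 ≤ 2.241 and Z2 > 2.241). At rho = 0 this is 0.8502 + (0.9064 − 0.8502) × 0.8502 = 0.898.

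| rho | Familywise error, either at .05 | Power, at least one at .05 | Power, both at .05 | Holm: given subscale | Holm: at least one |
|---|---|---|---|---|---|
| 0 | 9.75% | 99.1% | 82.2% | 89.8% | 97.8% |
| 0.5 | 9.1% | 97.1% | 84.2% | 89.0% | 94.2% |
| 0.6 | 8.8% | 96.4% | 84.9% | 88.7% | 93.3% |
| 0.7 | 8.4% | 95.7% | 85.6% | 88.5% | 92.2% |
| 0.8 | 7.8% | 94.8% | 86.5% | 88.2% | 90.9% |
| 0.9 | 7.0% | 93.6% | 87.7% | 87.8% | 89.2% |

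Powers in the table use the normal approximation.

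**Step 5. The single-step figure.** At .025 alone, power for one subscale is 85.0% (t-test 84.4%). That is Bonferroni power. It leaves out Holm's second step and should not be quoted as the power of a Holm procedure.

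**Step 6. One total score primary.** There is one test at .05, so Step 1 applies unchanged: 5% error and 90% power, if d = 0.5 is meant for that score.

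**The case against.** The strongest reply is that the Methods sections are the operative text, they use the singular, and an abstract's plural should not override them. If one HSCL-25 score is primary, nothing is inflated and the 90% stands. This is a fair reading, and it is why the point is stated conditionally. It does not remove the conflict, because no section names the single score and the instrument is described only through its two subscales.

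Two pieces of apparent evidence for two primaries are weak and are not relied on. The abstract's word subscales may be no more than the article's own expansion of the instrument's name, which recurs in the Table 1 footnote and the abbreviation list. Table 1 gives depression and anxiety separate rows, but it is a schedule of assessments and does not define endpoints.

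A reader might infer that the trial runs at 8-10% error and also falls short of 90% power. The article does not support that. It states no either-subscale rule, and its nearest statement of success joins depression and anxiety, which points towards requiring both. Under an either rule at .05, power for at least one subscale is 94-99%. Under a both rule, the error of the claim is not inflated. Even under the either rule, false claims of benefit alone rise from 2.5% to between 3.5% and 4.9%.

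Finally, a multiplicity method is often left to the SAP, which is not shown. That would answer a complaint about silence. Here, however, the article states a level for all analyses and gives conflicting counts of the primary outcome, so a SAP that adjusted alpha would itself have to be reconciled with this text.

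**Conclusion.** The concern holds as an unresolved definition with conditional consequences. The article is inconsistent on one versus two primary outcomes, fixes .05 for every analysis, and powers one unnamed comparison.

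- **Two subscales, either sufficient:** familywise two-sided error of about 8-10% for rho from 0 to 0.8, and about 7% at 0.9.
- **Two subscales, both required:** no inflation, but joint power of about 82-88% (about 85-86% at rho 0.6-0.8) in place of 90%.
- **One total score:** neither problem.

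The figures assume 86 evaluable per arm, d = 0.5 on each subscale and the stated range of correlations. The documents do not show which rule the sponsor intends, so none of these can be reported as the trial's actual error or power.

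**What to change.** Before data are analysed, choose one rule and use it consistently in the abstract and in the Primary Outcome, Sample Size and Statistical Analysis sections. The article's Results section reports that no analysis had yet been done, so at that point the choice could be made without knowledge of the results.

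- **(a) Either subscale suffices.** Test the two subscales at the 3-month follow-up by Holm at familywise two-sided 0.05. State power as about 88-89% for a given subscale and 91-93% for at least one (rho 0.6-0.8, assumed).
- **(b) Both required.** Test each at .05 and claim success only if both are significant. Restate joint power as about 85% (82-88% for rho 0 to 0.9).
- **(c) One score.** Name the HSCL-25 total as the sole primary outcome, make the subscales secondary, and say that d = 0.5 refers to the total. The 90% is kept.

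The sentence setting P<.05 for all analyses should then be limited to fit the rule chosen. None of the three options needs more participants. The cost is a few sentences and, under (a) or (b), a slightly lower stated power.

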**Results:**

The study was funded in January 2020 by the Research for Health in Humanitarian Crises Programme (Elhra) and recruitment for the trial started on July 16, 2023. As of November 15, 2023, we randomized 228 participants.

**Conclusions:**

This trial intends to contribute to the growing digital mental health evidence base by exploring technological solutions to address global public health challenges. Given the widespread use of technology globally, even in resource-constrained settings, and the high adoption rates among adolescents and young individuals, digital initiatives such as STARS present promising opportunities for the future of mental health care in low- and middle-income countries.

**Trial Registration:**

ISRCTN Registry ISRCTN10152961; https://www.isrctn.com/ISRCTN10152961

**International Registered Report Identifier (IRRID):**

DERR1-10.2196/54585

## Introduction

Mental disorders are one of the leading causes of disability worldwide, with an estimated 284 million and 264 million people affected by anxiety and depression, respectively [1]. The majority of mental disorders emerge between childhood and young adulthood, before the age of 25 years [2], with a median age of onset at 18 years [3]. The proportion of people with any anxiety disorder and the proportion of those with major depressive disorder that started before the age of 25 years is 7 out of 10 and 4 out of 10, respectively [3].

Although there exists a high prevalence of mental disorders, there remains an equally high treatment gap, with estimates of between 76% to 85% of people—in countries classified by the World Bank’s Development Indicators as “less developed” receiving no treatment [4]*.* This treatment gap is exacerbated by low expenditure on mental health services, with countries allocating on average less than 2% of their health care budgets to mental health*.* Compared to adults, young people are less likely to access mental health services due to reasons such as perceived stigma and limited knowledge about mental health [5]. Additionally, treatment is often designed for adults and may not be appropriate for younger adults [6]. There is a need for innovative approaches to increase access to mental health care. This need may be more pressing for conflict-affected populations, where the World Health Organization (WHO) estimates suggest around 1 in 5 people affected by conflict in the previous 10 years currently experience a mental disorder [7].

Research on the delivery of psychological interventions by nonspecialists, using task shifting, shows promising results [8]. Yet, while the evidence for the effectiveness of these interventions for youths is growing, difficulties remain in accessing evidence-based interventions, particularly in low- and middle-income countries (LMICs) [9,10]. This highlights the need for evidence-based psychological interventions that can be used in settings that are resource-pressured [11]. Such interventions should be suitable for scale-up, as well as being appropriate for diverse sociocultural groups. A number of these interventions have been developed for adult populations, with meta-analytical evidence suggesting their effectiveness [12]. However, there are fewer interventions that have been developed and trialed for younger populations with the resulting evidence being less concrete [9]. Digital solutions may be one way to mitigate some of the access and resource challenges for young people [8].

Digital mental health (also called e-mental health) interventions refer in part to the use of electronic devices such as smartphones to support the provision of mental health care. In high-income settings, some guided self-help interventions have been found to be as effective as face-to-face interventions in adults [13,14]. Additionally, these interventions have been shown to reduce symptoms of mental disorders in routine care [15]. Similar delivery models have also been shown to be effective in more resource-constrained, middle-income countries and with conflict-affected populations [16-18]. This compelling evidence has led to the inclusion of digital mental health interventions in a number of countries’ national mental health strategies and treatment guidelines [19]. In addition, WHO guidelines on mental health promotive and preventive interventions for adolescents and youths recommend the use of digital mental health interventions [20].

While the existing evidence for digital mental health interventions for youths suggests such interventions may be beneficial [21-23], the public availability of evidence-based interventions remains limited [9,24,25]. Additionally, while research on the efficacy of internet-delivered interventions is developing [21,26,27], studies beyond high-income English-speaking countries remain sparse, with the exception of China, where some studies have been completed [22,23]. However, digital mental health interventions may be a useful approach for increasing access to treatment because the use of electronic devices, internet, and social media continues to rise in LMICs, especially among youths [28-30]. This suggests the importance of developing, adapting, and determining the effectiveness of these types of interventions for younger populations, particularly in low- and middle-income and conflict-affected settings.

Implementation of digital mental health approaches is not without its challenges, as they introduce particular complexities associated with the use of digital platforms, such as the complexity and cost of building and maintaining some smartphone apps, which may lead to barriers in scale-up attempts [31]*.* A potential way to address these barriers is to explore the benefits of different delivery systems for online interventions. One such delivery method is using conversational agents, more commonly known as chatbots. Chatbots may provide a potential alternative and highly engaging method to deliver such interventions. Chatbots are text-based automated conversational agents that give the impression of speaking to a human, although the user is aware beforehand, that they are speaking with a computer program. They may use machine learning and respond to user inputs or use a decision tree format with users following a defined path. Preliminary studies exploring the effectiveness of chatbots on mental health outcomes are promising [32,33] and suggest they may be a practical way of providing mental health care as they can (1) use existing and widely available software infrastructures, and (2) may increase engagement due to the conversational nature of delivery.

For these reasons, the WHO has designed and developed a chatbot based on decision tree logic for youths, entitled Scalable Technology for Adolescents and Youth to Reduce Stress (STARS) [34]. This protocol outlines the first randomized controlled trial (RCT) aiming to test the effectiveness of STARS, a guided self-help mental health chatbot intervention among youths residing in Jordan, including Syrian refugees. This study builds and adds to the current literature as it aims to test a chatbot as an innovative delivery approach that may overcome some of the barriers and challenges involved in digital mental health interventions, within a middle-income, Arabic-speaking country, where specialist care for mental health is particularly limited and there is a high proportion of refugees per capita. Testing in this setting will demonstrate whether such an intervention aimed at youths may be a feasible model for scaling up much-needed services. This trial follows preliminary work on the development of the STARS intervention, including the cultural adaptation of STARS to the Jordanian context (not yet published), and a completed pilot trial to determine cultural acceptance and appropriate research methods. The primary aim of this study is to determine the effectiveness of the STARS intervention in alleviating symptoms of depression and anxiety among individuals aged 18-21 years residing in Jordan, compared to enhanced usual care (EUC). Secondary aims include assessing the effectiveness of STARS in improving levels of psychological distress, self-defined problems, general functioning, agency, and subjective well-being.

## Methods

### Design

We will conduct a 2-arm, single-blind, superiority RCT comparing the STARS intervention to EUC in 344 study participants. Multimedia Appendix 1 presents the Standard Protocol Items: Recommendations for Intervention Trials (SPIRIT) checklist and Multimedia Appendix 2 presents the trial registration data.

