**Figure 1 figure1:**
[figure not shown]
Study flowchart. K10: Kessler Psychological Distress Scale, 10-item version; STARS: Scalable Technology for Adolescents and Youth to Reduce Stress.

Participants will be directed to take part in the screening procedure after accessing the online software tool, Qualtrics, through the research project’s website and reading through the study information outlined earlier. As part of the screening procedure, participants will first be asked their country of residence and age, administered the K10, and administered the screening questions for imminent risk of suicide. Participants outside of Jordan, not between the ages 18-21 years, or screening negative on the K10 will be informed that they are not eligible for participation and will be invited to contact the implementing team if they have any questions or would like to receive information on psychosocial services available close to them. If participants are excluded due to screening positive for imminent risk of suicide, a message will appear that they may need additional mental health support along with signposting to a nationally recognized helpline.

If participants meet all inclusion criteria, they will be invited to provide their contact information (phone number and/or email address). Immediately after having completed the screening or on the next working day, participants will be contacted by a member of the research team to answer any questions regarding the study. Participants will then receive a personalized link to the baseline questionnaires.

All subsequent assessments will also be completed remotely by participants either on their own private devices, or devices that will be made available in private rooms at the IFH health care centers. The baseline assessment will include the following instruments: Hopkins Symptoms Checklist, 25 (HSCL-25) [39], WHO Disability Assessment Schedule 2.0 (WHODAS 2.0) [40], WHO-5 Well-Being Index (WHO-5) [41], Psychological Outcomes Profile (PSYCHLOPS) [42], and the agency subscale of the State Hope Scale (SHS-A) [43]. In addition, participants will be asked about their previous mental health care use both related to services and prescribed medicines. Following the baseline assessment, participants will be randomized to either receive STARS or EUC.

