### Randomization and Blinding

Participants will be randomized to receive either STARS or EUC at a 1:1 allocation ratio following the baseline assessment. The randomization sequence will be developed through Qualtrics software and will be automated and embedded in the baseline questionnaire, with participants having their group allocation conveyed to them immediately upon completion of the assessment. Given the high proportion of Syrian refugees and other populations residing in Jordan, randomization will be stratified on a 1:1 ratio (Jordanian or Palestinian vs Syrian or other nationalities). Given that questionnaires are self-administered online, the outcome assessments will not be blinded.

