### Limitations

Limitations to this study will be the potentially high attrition rates that are a common challenge in eMental health research [32] and the lack of long-term follow-up assessments (ie, beyond 3-month follow-up) to evaluate long-term outcomes of the intervention. Both interventions (STARS and EUC) require participants to have access to a device for intervention delivery (or to be willing to use one at a participating center), which may limit the generalizability of findings.

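### The trial is labelled single-blind in three places, but its blinding section says participants learn their arm and outcome assessment is unblinded, and the article names no blinded party

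*Protocol article*

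**What the plan says.** Three statements in the protocol article give the label:

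- Abstract, Methods: "A single-blind, 2-arm randomized controlled trial will be conducted nationally across Jordan".
- Methods, Design: "We will conduct a 2-arm, single-blind, superiority RCT comparing the STARS intervention to EUC in 344 study participants".
- Discussion, Brief Summary: "The goal of this trial is to conduct a single-blind, 2-armed RCT among 344 young adults".

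The section Randomization and Blinding gives the procedure. Randomization is automated inside the baseline questionnaire, "with participants having their group allocation conveyed to them immediately upon completion of the assessment". On assessment it says: "Given that questionnaires are self-administered online, the outcome assessments will not be blinded".

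Study Procedures confirms who does the rating: "All subsequent assessments will also be completed remotely by participants either on their own private devices", or on devices provided at the implementing organization's centers. The Discussion's Limitations paragraph begins "Limitations to this study will be the potentially high attrition rates" and goes on to the lack of longer follow-up and the need for a device. It does not mention blinding.

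**The concern.** A single-blind label normally tells the reader that either the participant or the outcome assessor does not know the allocation. Here those two roles fall to the same person, and the blinding section removes blinding from both. The label and the procedure therefore cannot be read together unless some third party is the one blinded, and the article names none.

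This matters because the primary outcome is a self-report symptom scale, where knowing one's arm can influence the answers. The arms are also easy to tell apart: a ten-session chatbot with five support calls against a website with psychoeducation and a list of services. A reader or evidence reviewer who classifies the design from the Abstract or the Design paragraph would credit the trial with a protection that its own blinding section says the outcome assessments lack. The article also links open-access release of the intervention to the results of this trial and a second one, so how the design is classified has consequences.

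**Working it through.** The check is mainly a comparison of statements, taking each party who could be blinded in turn.

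1. **Participants.** Ethical Considerations says that both interventions are described to them before screening. Randomization and Blinding says that the arm is shown when the baseline questionnaire is completed. They are not blinded from that moment on.
2. **Outcome assessors.** Study Procedures has participants complete all assessments remotely. The post-intervention assessment (8 weeks) and the follow-up (20 weeks) include the HSCL-25, K10, WHODAS 2.0, WHO-5, PSYCHLOPS and SHS-A, all self-completed. Randomization and Blinding states outright that assessment is unblinded. Baseline scores are entered before the arm is shown, so the contradiction concerns the two post-baseline time points. One of them is the primary time point.
3. **E-helpers.** They deliver the STARS calls and so know the arm. They rate no outcome, so this adds nothing to the risk in outcome measurement. It only rules them out as the blinded party.
4. **Research team.** Data Management gives the team access to the Qualtrics data, and the randomization sits in the Qualtrics baseline questionnaire. The team can also see chatbot data that exist only for STARS users, such as PHQ-2 scores and session completion dates. Nothing says that the team is masked.
5. **Analyst.** Statistical Analysis says nothing on masking. Data Management describes de-identification before storage, but that protects identity and does not conceal the arm. The article neither states nor rules out a masked analyst.

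Result: the article expressly unblinds the first two parties, describes work that reveals the arm to the third, and identifies neither of the last two as blinded. The label appears in exactly three places, and none says whom it refers to.

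**Does the label affect the sample size?** The planned figure was reproduced first. Inputs from Sample Size: d = 0.5, power 90%, two-sided alpha 0.05, attrition 50%.

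- Normal approximation: n per arm = 2(1.960 + 1.282)² / 0.5² ≈ 84.1, rounded up to 85.
- t-test version: 85.03, rounded up to 86 per arm, so 2 × 86 = 172 as stated. Power at 86 per arm is 0.903 (0.906 by the normal approximation).
- With attrition: 172 / (1 − 0.50) = 344, as stated.

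No term in this calculation depends on blinding, so correcting the label leaves 172 and 344 unchanged.

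**The case against.** The strongest reply has three parts.

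**The analyst may be the blinded party.** The term does not say who is blinded. The full protocol, the SPIRIT checklist, the registration data and any SAP are not shown, and masking at analysis is often specified there. This stands. A reader might infer that the trial has no blinding of any kind, and the article cannot show that. It shows only that no blinded party is identified and that outcome assessment is expressly unblinded. The reply does not remove the contradiction, though: a masked analyst leaves a self-reported outcome as unblinded as before, and a bare single-blind label does not convey that arrangement.

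**The fact is disclosed.** The blinding section states the lack of blinding and gives the reason, so a careful reader of the Methods would not be misled. This also stands, and it limits the harm to those who rely on the Abstract, the Design paragraph or the Discussion. Those are the places where designs are commonly classified, and the disclosure leaves all three uncorrected.

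**A label is not a bias.** Any effect of expectancy on self-report is there whatever the trial is called, and relabelling will not reduce it. That is right. A reader might infer a particular inflation of the treatment effect, but the documents give no figure from which to derive one. A reader might also infer that the control arm has no human contact, which would sharpen the expectancy argument. The article does not support that: the research team contacts all eligible participants before baseline, and reminder messages or calls are not limited to one arm. What differs is the support calls. That expectancy favors STARS is plausible but undocumented.

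**Conclusion.** The point holds as an internal contradiction about a core design property. Three statements claim single-blinding. The section on blinding says that participants know their arm and that outcome assessment is unblinded, and no blinded party is identified. It affects the post-baseline primary and secondary outcomes, which are all self-completed, and so the protection from bias that the trial can claim for them. It does not change the sample size, the mixed model or any trial procedure, and no magnitude of bias is asserted.

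The conclusion rests on the article alone. If an unseen document masks the analyst, the right description becomes open-label with a blinded analyst. The present wording would still need correcting, because it does not say so.

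**What to change.** 1. In the Abstract, Design and Brief Summary, replace the single-blind label with a description of an open-label trial with unblinded participant-reported outcomes, so that all three agree with Randomization and Blinding.
2. First establish whether the term was meant for the analyst. If it was, or if masking can still be introduced, run the primary analysis on masked arm codes, describe the trial as open-label with a blinded analyst, and name that role in Randomization and Blinding. The masked dataset should leave out variables that reveal the arm, such as PHQ-2 scores and session completion dates. The Results section says that no analysis had been done, so this was still possible when the article was written.
3. Add to the Limitations that the primary outcome is a subjective self-report measure completed by participants who know their allocation.

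Items 1 and 3 cost only wording. Item 2 costs the preparation of a masked dataset, which is minor. None of them requires a change to recruitment, data collection or the planned model.
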